## Research hypotheses

The hypothesis is that after the intervention, the mean scores of infant growth indicators, mothers' breastfeeding self-efficacy, and mothers' quality of life will increase compared to the control group.

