## Phase II: implementation of educational intervention

In this step a randomized controlled clinical trial will be design to assess the efficacy of the prepared protocol. Participants will randomly be allocated into two groups. In the experimental group we will implement our designed protocol, and the control group will not receive any intervention, but they are evaluated as the same as the experimental group. For ethical issues all educational material will offer at the end of the study (Fig. 1).

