### Study sample

This interventional randomized study will be conducted on mothers of infants who have been receiving maternity care at health centers in Yazd, Iran. According to the study of Araban et al. [24] and considering the level of significance (α = 0.05) and test power (β = 0.8) as well as the standard deviation of breastfeeding self-efficacy score which is 4.22 and 4.88 in case and control groups respectively, and in order to achieve a significant difference of at least 2.5 points in the mean score of breastfeeding self-efficacy in the intervention and control groups, and taking into account 10% of probable drop, the sample size is considered to be 57 subjects in each group using the following formula.$$n = \frac{{\left( {Z_{{1 - \frac{\alpha }{2}}} + Z_{1 - \beta } \left( {\sigma_{1}^{2} + \sigma_{2}^{2} } \right)} \right)}}{{d^{2} }}$$

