### Data analysis

To describe the state of the data, statistics such as the mean and standard deviation of the main research variables (growth rates of infants, breastfeeding self-efficacy, and quality of life) will be determined, and finally, by using SPSS version 22 the mean score of the main variables of the research before and after the intervention will be compared (if the data are normal) with paired t-test and (if the data are not normal) with the non-parametric Wilcoxon test. The randomized trial, will be the statistical analysis "per protocol". 95% confidence interval and P-value < 0.05 will be considered to investigate the effect of the intervention on the mean of the main research variables.

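### The t-test or Wilcoxon switch depends on a normality check, and its Wilcoxon branch does not test the mean that the plan sets out to compare

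*Protocol article*

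**What the plan says.** The Data analysis section names three families of "main research variables (growth rates of infants, breastfeeding self-efficacy, and quality of life") and says that their pre-test and post-test values "will be compared (if the data are normal) with paired t-test and (if the data are not normal) with the non-parametric Wilcoxon test". As the alternative to a paired t-test, the Wilcoxon test here must be the signed-rank test. The text does not say whether scores or changes are checked for normality.

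The same section ends with the inference that it promises: "95% confidence interval and P-value < 0.05 will be considered to investigate the effect of the intervention on the mean of the main research variables".

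The other places that define the target also speak of means. The Research hypotheses section expects that "the mean scores of infant growth indicators, mothers' breastfeeding self-efficacy, and mothers' quality of life will increase compared to the control group". The Study sample section is built on a difference of 2.5 points in the mean breastfeeding self-efficacy score. The Outcome measures section defines self-efficacy and quality of life as mean scores.

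**The concern.** The rule makes both the test and the quantity tested depend on the sample. The paired t-test asks whether the mean change is zero. The signed-rank test asks whether the changes are symmetric about zero, and the location it estimates is the pseudo-median. The two agree when changes are symmetric and differ when they are skewed. Skewed changes are also the ones that the rule sends to Wilcoxon, so the switch acts most often where the two tests answer different questions.

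Two things are at stake. A Wilcoxon p-value may be reported beside a mean and a confidence interval that it does not correspond to. And, read as a test of the mean, that p-value may reject too often or have too little power.

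**Working it through.** **Inputs from the protocol article.** Two-sided α 0.05, power 0.80, SDs 4.22 and 4.88, difference 2.5, dropout 10%, and 57 per group (all from Study sample).

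**The plan's own figure.** The standard formula for two means, which the printed expression is evidently meant to be, gives

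n = (1.960 + 0.842)² × (4.22² + 4.88²) / 2.5² = 7.849 × 41.62 / 6.25 = 52.3 per group.

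Adding 10% gives 52.3 × 1.1 = 57.5, and dividing by 0.9 gives 58.1. The stated 57 is reproduced to within rounding. It is a figure for a difference in means. With 10% lost, about 57 × 0.9 = 51 per group remain.

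**Assumptions that the article does not give.** The check is Shapiro-Wilk at 5%, applied to the changes. The changes are normal or centred gamma variables with true mean exactly zero. A gamma variable of shape k has skewness 2/√k. There were 4,000 simulated data sets per row, so the simulation error on a 5% rate is √(0.05 × 0.95 / 4000) = 0.3 percentage points.

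**Within-arm tests as written, n = 57, rejection of a true zero mean change:**

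| Changes | Skewness | Sent to Wilcoxon | Fixed t-test | Switch |
|---|---|---|---|---|
| Normal | 0 | 5% | 4.4% | 4.5% |
| Gamma, shape 8 | 0.71 | 46% | 5.1% | 7.2% |
| Gamma, shape 4 | 1.00 | 76% | 5.1% | 9.6% |
| Gamma, shape 2 | 1.41 | 97% | 5.3% | 14.8% |
| Exponential | 2.00 | 100% | 5.7% | 23.3% |

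Repeat runs put the last entry at 23-25%. With n = 51 the switch gives 7.0%, 8.4%, 14.5% and 23.5% for the four skewed rows, and the fixed t-test gives 5.1-6.8%.

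**Symmetric changes (n = 51).** With normal scores and normal changes, the switch and the fixed t-test both reject in 4.5%. With skewed scores but normal changes, and the check made on the scores, both reject in 5.1%. Power for a 1-point gain is then 0.646 with the switch and 0.657 with the t-test.

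**Between-group version.** With the same skewed shape in both arms (gamma shape 8 to exponential) and a t-test or Mann-Whitney switch, repeated simulations gave 4.7-5.9%. The fixed t-test gave 4.7-5.1%. The inflation is gone.

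**Mismatch with the mean.** As an invented illustration, let 20% of mothers gain 12.5 points and the rest nothing, with noise SD 3. The mean gain is 0.20 × 12.5 = 2.5. Within one arm of 51, the t-test has power 0.89 and the signed-rank test 0.62. The Wilcoxon location estimate is 1.7, against a true mean of 2.5. Compared between groups, the rank test has power 0.42 and the comparison of means 0.80. The check on the changes fails in nearly all such data sets, so the switch would almost always choose the rank test.

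**The case against.** The strongest reply is that normality-conditional testing is a declared and common convention, and that most of its apparent harm is harmless or belongs to another defect. Much of this stands.

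- **Which quantity is checked.** A reader might infer that the rule checks raw scores, which is the wrong quantity for a paired test. The article says only that the data are checked. A condensed article may leave that detail to the full protocol or analysis plan, so this cannot be charged as an error.
- **Different tests in different arms.** A reader might also infer that the two arms will often receive different tests on the same variable, and that this distorts the results. With normal data and a check on the changes, the chance is 2 × 0.05 × 0.95 = 9.5% per variable. Higher figures need the raw-score reading, and figures accumulated over many variables also need independence. That does not hold for growth indices built from the same measurements or for SF-36 domains from the same mother. Where changes are symmetric, a different test is mostly a different label.
- **Inflation belongs to the within-arm tests.** The 7-24% applies to tests of change inside one arm. It should not be read as the false-positive rate of a between-group claim.
- **The responder pattern is invented.** Nothing in the article suggests it, and it shows lost power rather than false positives.

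The reply leaves one thing unanswered. The section promises a p-value and an interval for an effect on the mean, and one of its two branches does not supply that p-value when changes are skewed.

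**Conclusion.** The point holds as a minor one. The plan states a rule under which the sample chooses the test, and the Wilcoxon branch does not match the mean-based hypothesis, sample size and confidence interval. For the within-arm tests as written with 57 per arm, the switch rejects a true zero mean change in about 7% (mild skew) to 24% (exponential) of trials, against about 5-6% for a fixed t-test. These figures rest on a Shapiro-Wilk check at 5% on the changes and on the gamma shapes used, neither of which comes from the article.

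The size depends on skewness. With symmetric changes there is almost no harm. With a between-group comparison and the same shape in both arms, the type I inflation disappears and only the mismatch with the mean remains. At 51 to 57 per arm the fixed t-test stays close to its nominal level (at most 6.8%, for exponential changes with n = 51), so the switch gives little protection that is needed.

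That both named tests compare before with after inside an arm, while the hypothesis compares arms, is a separate and larger matter. Correcting the switch alone does not settle it.

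**What to change.** Delete the normality condition. For each main variable prespecify one comparison of means with its 95% confidence interval, reported whatever the distribution. For coarse or bounded SF-36 domains use robust standard errors or a bootstrap interval for the same mean difference. Keep the rank test as a sensitivity analysis only. Any distribution check should look at changes or model residuals and must not select the main test.

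Make this change in the same edit as the correction of the within-group comparison. A single prespecified between-group model of the post-test mean, adjusted for baseline, would serve both. It should be fixed before outcome data are analysed.

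The cost is about one sentence in the Data analysis section, with no extra participants or data and no change to the 57 per group. The downside is some loss of efficiency if an outcome is heavily skewed, which the sensitivity analysis would show.

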### Virtual educational support sessions

All mothers of the intervention group will join the WhatsApp group, which is managed by the researchers. Additionally, other members of the virtual group include a midwife, a nurse, a healthcare provider and a family physician for answering the specialized questions of the mothers. Accordingly, about their questions, the mothers will have access to nurses, physicians and midwives.

In this group, 2 days a week, an educational program will be provided by the researcher in the form of educational packages related to breastfeeding, growth and development, vaccination, health and nutrition and other care for children under one year of age for two months. The educational content has been shown in Table 1. These packages will be sent to mothers based on the latest references from pediatric nursing books approved by the Ministry of Health and the family physician. Two days after sending the educational materials to the mothers, the researcher (pediatric nurse) will provide the mothers with additional explanations about the educational content for 40 min and the mothers will ask their questions. In this study, the control group will confirm the demographic information form and the consent form, and they will complete the quality of life and breastfeeding self-efficacy questionnaires before and after the intervention, and during the intervention, they will benefit from the routine services of health centers. These services include visiting the health center in person and checking the growth and development of the infant and receiving care information from the health team members.

**Table 1 Tab1:** Educational content

Educational program	Educational content	How to provide education	Audience
Educational package			
Newborn	Breastfeeding methods (time and duration of breastfeeding); milking and storing breast milk; bathing the infant; vaccination and aftercare; umbilical cord care; change of clothes; burping; methods of preventing sudden infant death syndrome; how to use supplements; Thyroid check-up (hypothyroidism training); education of danger and safety symptoms and the need for seeing a physician; and audiometry	The educational program will be offered two days a week and for two months in the form of an educational package which will be sent to the virtual group	Mothers of infants

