### Peer group experiences

In addition to virtual sessions, the mothers of this group will be able to share their experiences about the growth and development of their infants in this space for three months. At the beginning of the study, the mothers will be informed that the prescription of chemical, herbal, and traditional medicines is against the rules of the research plan and in case of violating these rules, they will be removed from the group. Sharing the experiences of mothers is limited to the issues of growth and development of a healthy child. The researcher and family physician will control all the messages of the intervention group members and prevent the mothers from confusion by providing them with correct guidance. Moreover, in case of illness and any clinical problems for the infant, it is recommended that mothers see a specialist in person.

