### Exclusion criteria

The diagnosis of chronic illness of the baby, the death of the baby, and the unwillingness of the mother to continue cooperation are the exclusion criteria.

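### An undefined per-protocol analysis is the only one stated for a randomised superiority trial; it can select mothers differently by arm, so the estimate can be biased

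*Protocol article*

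**What the plan says.** All references are to the protocol article.

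- **Analysis population.** Data analysis states "The randomized trial, will be the statistical analysis 'per protocol". No section mentions an intention-to-treat or as-randomised analysis, and no section says which mothers count as following the protocol.
- **Design and question.** Under Phase II, "Participants will randomly be allocated into two groups". The Research hypotheses section expects that "mothers' breastfeeding self-efficacy, and mothers' quality of life will increase compared to the control group", which is a superiority claim against control.
- **Who has something to adhere to.** Under Virtual educational support sessions, "All mothers of the intervention group will join the WhatsApp group, which is managed by the researchers". Packages arrive twice a week for two months, and peer exchange runs for three. Controls receive routine health-centre services. The Discussion lists neglect of the packages among the expected limitations.
- **Removal rule.** Under Peer group experiences, mothers are told not to prescribe medicines in the group and that "in case of violating these rules, they will be removed from the group".
- **Exclusion criteria.** These are a diagnosis of chronic illness in the baby, the death of the baby, and a mother who no longer wishes to take part: "the unwillingness of the mother to continue cooperation are the exclusion criteria". All three arise after enrolment, and none is limited to one arm.

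**The concern.** Randomisation makes the two groups comparable as they were drawn. A per-protocol set is formed from what happens afterwards, and here the arms do not offer the same opportunities to fail. A control mother cannot neglect packages she is not sent or be removed from a group she is not in. Almost any adherence-based definition would therefore filter the intervention arm on engagement and leave the control arm largely unfiltered.

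If mothers who disengage from a programme lasting months tend to have lower self-efficacy or quality of life, the remaining intervention mothers will look better than the controls even if the programme does nothing. In a superiority trial that is the anti-conservative direction. Because the set is undefined, its membership could also be settled after outcomes are known. With no as-randomised analysis beside it, nothing in the plan would show whether the result depends on who was left out.

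**Working it through.** **Inputs from the Study sample section.** The standard deviations are given as "standard deviation of breastfeeding self-efficacy score which is 4.22 and 4.88 in case and control groups respectively". The target difference is 2.5 points on the breastfeeding self-efficacy scale, alpha is 0.05 (two-sided, from the Z term in the formula), power is 0.80, the drop allowance is 10%, and the stated size is 57 per group.

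**Step 1: the plan's own figure.** The standard formula is n = (z₁₋α/₂ + z_power)² (s₁² + s₂²) / d².

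- s₁² + s₂² = 17.81 + 23.81 = 41.62.
- (1.960 + 0.842)² = 7.849.
- n = 7.849 × 41.62 / 6.25 = 52.27.
- Adding 10% gives 52.27 × 1.1 = 57.5. Dividing by 0.9 gives 58.1.

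The stated 57 is consistent with this, so the inputs can be used as they stand.

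**Step 2: bias from one-sided selection.** The protocol gives neither the share of mothers excluded nor the link between exclusion and outcome, so both are assumed. Let a share f with the lowest engagement be dropped from the intervention arm only, and let engagement correlate ρ with the post-test score. With no true effect, the expected spurious gain is

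bias = s₁ × ρ × φ(z_f) / (1 − f).

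- f = 10%: φ/(1 − f) = 0.1755/0.9 = 0.195. At ρ = 0.5 the bias is 4.22 × 0.5 × 0.195 = 0.41.
- f = 20%: φ/(1 − f) = 0.2800/0.8 = 0.350. At ρ = 0.5 the bias is 4.22 × 0.5 × 0.350 = 0.74.

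| Share dropped, intervention arm only | ρ = −0.3 | ρ = 0 | ρ = 0.3 | ρ = 0.5 |
|---|---|---|---|---|
| 5% | −0.14 | 0 | 0.14 | 0.23 |
| 10% | −0.25 | 0 | 0.25 | 0.41 |
| 20% | −0.44 | 0 | 0.44 | 0.74 |

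Against the 2.5-point target, 0.41 is 16% and 0.74 is 30%.

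**Step 3: false-benefit rate.** This is for an unadjusted between-arm comparison of post-test scores, with about 51 per group after 10% loss (57 × 0.9 = 51.3).

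- SE = √(41.62/51) = 0.903.
- f = 10%, ρ = 0.5: 1 − Φ(1.96 − 0.41/0.903) = 6.6%.
- f = 20%, ρ = 0.5: 1 − Φ(1.96 − 0.74/0.903) = 12.7%.
- With no bias: 2.5%.

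Keeping all 57 controls and 57(1 − f) intervention mothers instead gives two-sided type I error of 7.6% and 13.0%, so the choice of standard error matters little.

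**Step 4: the same loss in both arms.** If each arm loses 10% by the same mechanism, the net bias is (4.22 − 4.88) × ρ × 0.195, which is −0.04 at ρ = 0.3 and −0.06 at ρ = 0.5. That is close to nil. Unequal selection between the arms causes the problem, rather than loss as such.

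**Step 5: sample size under the fix.** At d = 2.5 and a pooled SD of 4.56, power is 0.833 with 57 per group and 0.790 with 51, before any dilution by non-adherent mothers.

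**The case against.** The strongest case on the other side is that the direction is not in the documents. A reader might infer that the result will be biased towards the programme. The protocol does not support that: it gives no exclusion share and no relation between exclusion and outcome, and Steps 2 and 4 show that the bias can be positive, nil or negative. This objection stands.

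A reader might also infer that mothers removed under the medicines rule leave the analysis. The text removes them only from the virtual group. Their leaving the analysis is an inference from the undefined per-protocol wording. The rule is also narrow, and mothers who post advice may be more confident than average, so dropping them could work against the programme. This stands too.

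The exclusion criteria apply to both arms. That they would act unequally is a supposition about behaviour and not something the criteria say.

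The illustration also models things the plan does not state. No section sets an engagement threshold, and the 10% in the Study sample section is an overall drop allowance rather than a one-arm exclusion. Data analysis names before-after paired tests, not a between-arm test. For pre-post change, part of the level bias would cancel if engagement relates similarly to both scores. The figures cover self-efficacy only; infant growth is taken from health records. They should therefore be read as a scale and not as a forecast.

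None of this defends the analysis choice itself. The per-protocol sentence is a positive statement and not a detail left out of a condensed article. Any contrast with control made to answer the stated hypothesis would use the same selected mothers.

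**Conclusion.** The point holds as a risk built into the plan. An undefined per-protocol analysis is the only one stated for a randomised superiority trial, and adherence, neglect of packages and removal from the virtual group can occur in one arm only. The protection of randomisation is given up, and the estimate can be biased, plausibly but not necessarily towards the programme.

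Under moderate assumptions (ρ of 0.5, with 10% to 20% dropped from the intervention arm only), the distortion is a sizeable fraction of the target difference, and the false-benefit rate is roughly 2.6 to 5 times its nominal value. Those assumptions are not in the protocol. The case for changing the plan does not depend on the sign or the exact size.

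**What to change.** **Data analysis.** Make the primary analysis an as-randomised (intention-to-treat) between-group comparison. Each randomised pair is analysed in the arm drawn, whatever the mother's adherence or removal from the virtual group. Handle missing post-tests with a baseline-adjusted model or multiple imputation. Define the per-protocol set before outcomes are seen and keep it as a supportive analysis.

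**Follow-up.** Seek post-test questionnaires from non-adherent or removed mothers who still consent. Their phone numbers are already obtained at recruitment, and growth measurements come from the health card or record.

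**Exclusion criteria.** State that non-adherence, or a new diagnosis of illness in the baby, does not by itself take the pair out of the analysis set. Report infant deaths and withdrawals of consent by arm. Do not impute a post-test score after a death, because such a score would have no sensible meaning.

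**Cost.** The cost is revised wording, some extra follow-up contact and a possibly diluted estimate. This point alone does not require a change to the 57 per group.

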### Data collection method

#### Quality of life questionnaire

The SF-36 Quality of Life Questionnaire is a general questionnaire for assessing the quality of life of individuals; it assesses the quality of life of individuals in 8 domains of physical function, limitations caused by physical problems, social functioning, physical pain, and mental health, limitations caused by mental problems, vitality and general health. The score of each domain is calculated independently and ranges from zero (the worst condition) to 100 (the best condition). Questions of the mentioned dimensions are as follows: physical function (questions 3 to 12); limitation caused by physical problems (13 to 16); social functioning (2, 20 and 32), physical pain (21 and 22), mental health (24 to 28 and 30); limitations caused by mental health problems (17 to 19), vitality (23, 27, 29, 31) and general health (1, 33 to 36). The reliability of this questionnaire has been calculated to be 0.89 and 0.92 by retest and Cronbach's alpha respectively [14].

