### Outcome measures

#### Breastfeeding self efficacy of mothers

The mean score of Breastfeeding Self efficacy of mothers will be measured using a questionnaire BSES-SF Dennis in the pre-test and post-test phases.

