#### Quality of life of mothers

The mean score of the Quality of Life of mothers will be measured using a questionnaire SF36 in the pre-test and post-test phases.

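### Three outcome families are all called main and judged at P < 0.05 with no declared primary, although only breastfeeding self-efficacy sets the sample size

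*Protocol article*

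**What the plan says.** The Data analysis section names the "main research variables (growth rates of infants, breastfeeding self-efficacy, and quality of life" together and applies one criterion to them: "P-value < 0.05 will be considered to investigate the effect of the intervention on the mean of the main research variables". The Research hypotheses section joins the three in a single statement: "the mean scores of infant growth indicators, mothers' breastfeeding self-efficacy, and mothers' quality of life will increase compared to the control group". The Outcome measures section lists them side by side under separate subheadings, without ranking.

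The number of scores per family is only partly settled:

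- **Breastfeeding self-efficacy:** one score. "The mean score of Breastfeeding Self efficacy of mothers will be measured using a questionnaire BSES-SF Dennis".
- **Quality of life:** the Quality of life questionnaire section describes eight SF-36 domains and says "The score of each domain is calculated independently and ranges from zero (the worst condition) to 100 (the best condition". It defines no total. The Outcome measures section speaks in the singular: "The mean score of the Quality of Life of mothers will be measured using a questionnaire SF36".
- **Infant growth:** five indices, listed under Infants' growth status (weight for age, height for age, weight for height, head circumference for age, BMI for age).

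The Study sample section uses only one of these outcomes. It seeks a "significant difference of at least 2.5 points in the mean score of breastfeeding self-efficacy in the intervention and control groups", with standard deviations of 4.22 and 4.88, alpha 0.05, power 0.8 and a 10% allowance for dropout, and arrives at 57 per group.

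**The concern.** The Study sample section treats self-efficacy as the outcome that carries the trial. The Data analysis section gives all three families the same standing and the same 0.05. Nothing connects the two sections by saying which result decides the conclusion.

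Followed as written, the plan leaves the chance of at least one false positive across the main outcomes above 5%. A null result on self-efficacy with a nominally significant result on one growth index or one quality-of-life score could be reported as an effect on a main variable. The plan also leaves open whether quality of life is one test or eight, so that choice could be made with the data in view.

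**Working it through.** **1. The plan's own figure.** The inputs are those in the Study sample section. The formula as typeset lacks the square and has misplaced brackets, so the standard form is used:

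n = (z₀.₉₇₅ + z₀.₈₀)² × (σ₁² + σ₂²) / d²

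- σ₁² + σ₂² = 4.22² + 4.88² = 17.81 + 23.81 = 41.62
- (1.960 + 0.842)² = 7.849
- n = 7.849 × 41.62 / 2.5² = 52.27 per group
- 52.27 × 1.10 = 57.5, against 57 stated

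The sample size is thus reproduced from self-efficacy alone at an unadjusted two-sided 0.05.

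**2. Number of tests.**

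- One per named family: 3
- BSES-SF 1 + quality of life 1 + growth 5 = 7
- BSES-SF 1 + SF-36 domains 8 + growth 5 = 14

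**3. Family-wise error with independent tests and no true effect on any outcome.** The formula is 1 − 0.95^m.

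- m = 3: 1 − 0.857 = 14.3%
- m = 7: 1 − 0.698 = 30.2%
- m = 14: 1 − 0.488 = 51.2%

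**4. Allowing for correlation.** The article gives no correlations, so these are assumptions. Two-sided tests, no true effect, one equal correlation between every pair of tests:

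| Tests | 0 | 0.3 | 0.5 | 0.7 | 0.8 |
|---|---|---|---|---|---|
| 3 | 14% | 14% | 13% | 11% | 10% |
| 7 | 30% | 27% | 23% | 18% | 15% |
| 14 | 51% | 44% | 35% | 25% | 20% |

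If the fourteen tests are correlated only within their own family, the figures are about 47%, 42% and 34–35% at correlations of 0.3, 0.5 and 0.7. At 0.8 within families and 0.3 between them, the figure is about 29%. Over both structures, fourteen tests give about 20–47%.

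**5. Cost of the remedies, on the inputs of step 1.**

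- One primary outcome at 0.05: error on the primary is 5%, and 57 per group stands.
- Splitting alpha over three tests (0.05/3 = 0.0167): 70 per group before dropout, 78 after (70/0.9).
- Splitting over fourteen (0.05/14 = 0.0036): 94 before dropout, 105 after (94/0.9).
- With 10% lost from 57, 51 remain per group. Power for the 2.5-point difference is then about 79% at 0.05, 65% at 0.0167 and 44% at 0.0036.

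**The case against.** **A reader might infer that a false positive is about as likely as not.** The article does not support that. The 51% needs fourteen tests, all independent, and no effect anywhere. The SF-36 domains come from one mother's questionnaire, and the growth indices share the same weight and height measurements, so independence is implausible. The statement that "The score of each domain is calculated independently" describes how the questionnaire is scored. It is not a plan for eight hypothesis tests, and the singular wording in the outcome list allows seven tests in all, with at most about 30%.

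**A reader might also infer that any one significant score makes the trial positive.** The article states no such rule. Its hypothesis is worded as a conjunction. If every outcome had to succeed, false positives would not be inflated and the cost would fall on power. But the article does not state that rule either, so the gap remains.

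**Self-efficacy is arguably the primary outcome already.** It alone sets the sample size and it stands first in the outcome list. All three families are also specified in advance, so the risk is selective emphasis and not the invention of outcomes. That is fair. Even so, powering an outcome does not tie the conclusion to it, and the Data analysis section calls all three main.

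**Detail may sit in an analysis plan that is not shown.** For adjustment methods this stands, and their absence here is no fault. The point rests on what the article does state: equal standing for three families and 0.05 for all.

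**The tests named are paired before–after tests.** The figures above assume valid tests of the between-group hypothesis. The choice of paired tests is a separate matter and does not remove this one.

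**Conclusion.** The point holds in a limited form. The article gives three families equal standing, judges them at P < 0.05 and declares no primary outcome, while its sample size rests on breastfeeding self-efficacy alone. With no true effects and independent tests, the family-wise error is about 14%, 30% or 51% for three, seven or fourteen tests. These are upper figures for positively correlated tests. At assumed correlations of 0.3–0.8, fourteen tests give about 20–47%, and even three tests at 0.8 give about 10%, twice the nominal level.

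The number of tests and the correlations are the uncertain inputs, because the article fixes neither. The conclusion does not depend on them: on every count and correlation examined, the error exceeds 5% unless success requires all outcomes together, which the article does not say. It should be corrected before analysis.

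**What to change.** In the Data analysis and Outcome measures sections:

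- Name the BSES-SF score, compared between the randomised groups, as the single primary outcome tested at two-sided 0.05. This follows from the Study sample section.
- State that the trial's conclusion rests on that result.
- Make SF-36 and the growth indices secondary. They can be tested in a fixed order after BSES-SF, tested with Holm adjustment after it, or labelled exploratory. Any of these is acceptable.
- Say whether quality of life means one score or eight domain scores.

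The cost is a few sentences. The 57 per group and the power for BSES-SF are unchanged. The downside is that the secondary outcomes carry less weight or face a stricter threshold. Splitting alpha equally would instead raise the requirement to 78 per group for three tests or 105 for fourteen, dropout included, so naming one primary outcome is the cheaper course.
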